#### Criteria for premature termination for the whole trial

The sponsor representative is entitled to interrupt or prematurely terminate the entire clinical trial, e.g., if:
The recruitment rate is inadequateSerious, unresolvable problems arise with the quality of the data collectedUnacceptable risks have arisen (decision after a new risk-benefit assessment has been made)New scientific findings during the duration of the clinical trial do not allow it to be continuedThere could be a risk to patient safety

#### Provisions for post-trial care

The further treatment of participants after the regular end of their participation, after withdrawal of their consent, or in case of discontinuation of the treatment or the clinical trial is carried out according to the national standards defined in guidelines. Medications for relapse prophylaxis, which were already taken during the clinical trial as concomitant medication in permitted dosage and not newly initiated, will be continued in unchanged dosage according to the standards. Further treatment will be continued at the study site or with the previously treating specialist.

### Sample size

Sample size calculations were performed for the primary outcome remission rates 12 weeks post first FMT/FMFT/placebo. The sample size calculation is based on a 2×3 table *χ*^2^ test as implemented in nQuery Advisor 7.0 (*χ*^2^ test of equal proportions in G groups (equal *n*’s)) even though a more complicated model will be used for the confirmatory analysis. Based on this, we estimate the remission rates 12 weeks post first FMT/FMFT to be *π*_FMT_ ≈30% or π_FMFT_ ≈30% while *π*_Placebo_≈5% are expected under placebo. To detect such a clinically relevant benefit at an overall power of 1 – *β* = 0.8 for a global significance level of *α* = 0.05 (two-sided), a sample size of *n* = 3 × 40 = 120 is required for the confirmatory analysis. To account for a potential dropout rate of 30% overall and/or lower power of the more advanced analysis model, the total sample size is *n* = 3 × 58 = 174 patients.

Table 1 shows the impact of slightly altered planning assumptions regarding the true rates on the global power. Moreover, the table also depicts power estimates for the joint test of FMT/FMFT against placebo and the two-group tests of FMT vs. placebo, FMFT vs. placebo (two group continuity corrected *χ*^2^ test of equal proportions; unequal and equal *n*). As similar rates are expected for FMT and FMFT, no power estimates are provided for this comparison.

**Table 1 Tab1:** Statistical power analysis

True rates [%]			Sample size per group (including dropouts)^a^	Power for the respective test setting [%]		
*π*_FMT_	*π*_FMFT_	*π*_Placebo_		Global test^b^	FMT and FMFT vs. placebo	FMT or FMFT vs. placebo
30	30	5	58	93	98	92
30	40	10	58	92	95	69 rsp 95
40	40	10	58	96	99	95

^a^Resulting in a total sample size would be 3 × 58 = 174, 3 × 93 = 279, and 3 × 50 = 150 patients to be randomized

^b^The increased power (i.e., a power larger than 80%) results from the inclusion of dropouts in the analysis

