### Outcomes

#### Primary outcome

The primary outcome will be clinical remission at week 12 post first transfer of FMT or FMFT, defined by Mayo score ≤ 2 and without any subscore >1; additionally, patients who are unavailable at follow-up week 12 will be included as non-responders (i.e., counted no remission). The Mayo Score/Disease Activity Index (DAI) is a validated scoring system for the assessment of ulcerative colitis activity including stool frequency, rectal bleeding, endoscopic findings, and physician’s global assessment [21].

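### Table 1's powers count dropouts at full remission rates, while the sample-size inflation treats them as lost and the endpoint counts them as failures; the plan must say which rates 30/30/5% are

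*Protocol article*

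**What the plan says.** All places are in the protocol article.

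- **Sample size, method.** "The sample size calculation is based on a 2×3 table" chi-square test with equal groups. The combined and pairwise powers come from a two-group continuity-corrected chi-square "test of equal proportions; unequal and equal" group sizes. The level is 0.05 two-sided and the target is 80% overall power.
- **Sample size, numbers.** Rates of 30% (FMT), 30% (FMFT) and 5% (placebo) lead to 3 × 40 = 120. The total becomes 3 × 58 = 174: "To account for a potential dropout rate of 30% overall and/or lower power of the more advanced analysis model".
- **Table 1, row 1.** "30 30 5 58 93 98 92": the three rates, the group size, then power for the global test, both active arms together versus placebo, and either active arm versus placebo.
- **Table 1, footnote b.** "The increased power (i.e., a power larger than 80%) results from the inclusion of dropouts in the analysis".
- **Primary outcome.** "patients who are unavailable at follow-up week 12 will be included as non-responders (i.e., counted no remission").

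**The concern.** Three statements about the same patients do not fit together. The step from 40 to 58 treats a dropout as someone who contributes no outcome. Table 1 treats that person as someone who remits at the full rate for the arm. The endpoint definition treats the same person as a failure.

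Footnote b adds a mechanism. It says that power rises above 80% because dropouts are included. Under the endpoint rule they are included as failures in every arm, which multiplies each rate by the proportion observed and shrinks the difference. The extra patients therefore cannot bring the gain that Table 1 shows, unless the rates already allow for them.

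What is at stake is the published justification of the sample size. A reader of a null FMT or FMFT result would take it that the comparison had 92% power, when under one reading of the plan's assumptions it had about 74%.

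**Working it through.** **Inputs.** From Sample size and Table 1: rates 30/30/5%, 30/40/10% and 40/40/10%; n = 58 per arm (116 for the two active arms together); two-sided level 0.05; dropout 30%. From Primary outcome: unavailable patients count as no remission.

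**Formulas.**
- Global test: noncentral chi-square with 2 df, λ = n·Σ(pᵢ − p̄)² / [p̄(1 − p̄)].
- Two-group test, placebo n and active k·n, difference d: the continuity correction reduces n to n′ = n·[1 − (1 + 1/k)/(2dn)]². Power is Φ{[d√n′ − 1.96·s₀]/s₁}, with s₀² = p̄(1 − p̄)(1 + 1/k), s₁² = p₀(1 − p₀) + p₁(1 − p₁)/k, where p₀ is the placebo rate, p₁ the active rate and p̄ the weighted mean rate.

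**Step 1: reproduce the plan.** For 30/30/5%, p̄ = 0.2167, Σ(pᵢ − p̄)² = 0.04167 and p̄(1 − p̄) = 0.1697.
- n = 40: λ = 9.82, power 80.8% (39 per arm gives 79.7%). So 40 is confirmed, and 40/0.7 = 57.1 rounds up to 58.
- n = 58: λ = 14.24, power 93.2%.
- Combined (k = 2, d = 0.25): n′ = 52.2, power 98.2%.
- Pairwise (k = 1, d = 0.25): n′ = 50.3, power 92.2%.

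This matches 93/98/92. Rows 2 and 3 give 92.5/95.0/69.7 and 95.2, and 96.3/99.1/95.2, all within a point of the table. Table 1 therefore uses all 58 per arm at undiluted rates.

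**Step 2: apply the endpoint rule.** Suppose the rates hold in patients seen at week 12 and 30% of each arm is unavailable. Then 30/30/5% × 0.7 = 21/21/3.5%, still with 58 per arm.
- Global: p̄ = 0.1517, Σ(pᵢ − p̄)² = 0.02042, p̄(1 − p̄) = 0.1287, λ = 9.20, power 78.0%. By this formula 61 per arm would give 80%.
- Combined (d = 0.175): n′ = 49.8, power 86.3%.
- Pairwise (d = 0.175): n′ = 47.1, power 74.4%.

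| Row (rates) | Table 1: global / combined / pairwise | 30% unavailable, counted as failures |
|---|---|---|
| 30/30/5 | 93 / 98 / 92 | 78 / 86 / 74 |
| 30/40/10 | 92 / 95 / 69 and 95 | 76 / 77 / 48 and 79 |
| 40/40/10 | 96 / 99 / 95 | 83 / 90 / 79 |

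**Step 3: vary the proportion unavailable (row 1).** 10%: 90/96/88. 20%: 85/92/82. 30%: 78/86/74.

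**Step 4: check the approximation.** The planning formulas are conservative. Simulated power of the Pearson global test is 98.0% undiluted and 87.7% diluted. Exact power of the continuity-corrected tests goes from 98.7% to 89.9% (combined) and from 94.3% to 78.3% (pairwise). The pairwise comparisons lose most on either basis.

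**The case against.** The strongest reply is that Table 1 is right. The section says its calculations concern the remission rates of the primary outcome, and the table heads them as true rates. The primary outcome already includes the non-responder rule, so 30/30/5% can be read literally as rates with failures counted. All 58 per arm are then analysed at those rates, 93/98/92% is correct, and footnote b means only that 58 rather than 40 enter the analysis. This reading stands as a possibility. It has a cost: if failures are already inside the rates, 40 per arm is enough and dropout gives no reason to go to 58. The division by 0.7 therefore favours the other reading but does not settle it.

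Two further points also stand in part. The 30% is a potential, overall figure, and the inflation may partly be a reserve for the mixed model. Also, the endpoint rule covers only patients unavailable at week 12: someone who interrupts treatment may still be assessed, and someone never treated is outside the full analysis set. So 30% failures in every arm is the upper end of the range. The reserve for the model does not explain Table 1, however, because its powers come from plain chi-square tests and footnote b credits dropouts.

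A reader might infer that the true powers simply are 78/86/74%, or that the trial misses its power target. The documents do not support either. The first depends on an unstated meaning of the rates. The second is a gap of 2 points on a conservative formula, and the simulated Pearson test stays near 88%. Nor do these figures show the power of the planned mixed model with its site and stratum terms.

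**Conclusion.** The concern holds in conditional form. The sample-size section is inconsistent whichever way the rates are read. If they refer to patients seen at week 12, Table 1 and footnote b are wrong. If they already count unavailable patients as failures, the dropout argument for 120 to 174 is wrong.

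On the first reading, with 30% unavailable in each arm and the plan's own formulas, row 1 falls by 15, 12 and 18 points (93 − 78, 98 − 86, 92 − 74). The global test ends close to its 80% target. The pairwise comparisons, for which the plan sets no power target, carry the main loss; FMT versus placebo in row 2 falls from 69% to 48%. With 10% unavailable the row 1 losses are only 2 to 4 points.

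Severity is moderate: no test, endpoint, error rate or sample size changes.

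**What to change.** Keep N = 174. State in Sample size whether 30/30/5% already counts patients unavailable at week 12 as failures. Then:

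- **If it does not:** restate the Table 1 powers at the diluted rates over 10% to 30% dropout (row 1 from 90/96/88 to 78/86/74) and remove footnote b.
- **If it does:** keep the Table 1 powers, remove dropout as the reason for going from 120 to 174, and reword footnote b to say that power exceeds 80% because 58 rather than 40 per arm are analysed.

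The cost is a rewording of one section and one table, with no extra patients. The drawback is that the stated power may become less favourable.

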### Statistical analysis

The main analysis will be conducted in the full analysis set according to the intention-to-treat principle. Remission rates will be compared with a two-step hierarchical testing procedure. In a first step, a generalized linear mixed model (GLMM) with fixed effects treatment and steroid/thiopurine stratum and random effect site will be applied to test the null hypothesis H_0_ that no difference in remission rates will be observed between the groups against the alternative in which there will be a difference between the groups. In case of rejection of H_0_, the following tests will be performed in a hierarchical order:
The FMFT and FMT group combined versus placeboFMT versus placeboFMFT versus placeboFMFT versus FMT

by means of Wald statistic on a two-sided significance level of 0.05. The significance level is met by this hierarchical testing approach.

Further sensitivity analyses in a per-protocol set, explorative subgroup analyses according to stratification levels, and analyses of secondary parameters with a respective GLMM approach are described in detail in the study protocol.

In principle, all data will be analyzed at least by descriptive statistics, i.e., number of available and missing data, mean, standard deviation, minimum, quartiles, and maximum for metric data and frequency analysis for categories.

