### Patient population

#### Inclusion criteria

18–75 years oldWritten informed consentPrior endoscopic confirmation of active UC of at least 6 months *and* with a minimum disease extent of 15 cm from the anal vergeHaving active disease, defined with a Mayo Score between 4 and 10 and Mayo endoscopic subscore >1 at study entryMay be receiving the following drugs (subjects on these therapies must be willing to remain on stable doses for the noted times)Oral 5-ASA compounds provided the dose prescribed has been stable for at least 4 weeks prior to randomization; the dose must be stable for the first 12 weeks after randomizationAzathioprine, 6-MP, or MTX provided the dose prescribed has been stable for 8 weeks prior to randomization; the dose must be stable for the first 12 weeks after randomizationOral corticosteroid therapy (prednisone prescribed at a stable dose ≤ 20 mg/day or budesonide prescribed at a stable dose of ≤ 9 mg/day) provided the dose prescribed has been stable for 2 weeks prior to randomizationTopical therapy (foams, enema) with mesalazine or budesonide: the dose prescribed has been stable for 2 weeks prior to randomizationComplete vaccination against SARS-CoV-2 as recommended by the STIKOAbility to understand and willingness to sign informed consent document in patients whom the investigator believes can and will comply with the requirements of the protocol

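### Adding baseline Mayo score to the primary model would be a low-cost improvement of modest, uncertain size; its omission is not an error

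*Protocol article*

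**What the plan says.** All references are to the protocol article.

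- **Statistical analysis.** The primary model is a GLMM with "fixed effects treatment and steroid/thiopurine stratum and random effect site". A global test comes first. If it rejects, Wald tests follow in fixed order, "on a two-sided significance level of 0.05": both active arms combined against placebo, FMT against placebo, FMFT against placebo, FMFT against FMT. The section refers the reader to the full protocol for sensitivity, subgroup and secondary analyses, but not for the primary model.
- **Primary outcome.** Remission at week 12 is "defined by Mayo score ≤ 2 and without any subscore >1", and "patients who are unavailable at follow-up week 12 will be included as non-responders".
- **Inclusion criteria.** Active disease is "defined with a Mayo Score between 4 and 10".
- **Randomization.** Two descriptions of the stratification are given, one using previous biologics and one using steroid/thiopurine use, each with site. Neither uses the Mayo score.
- **Sample size.** The calculation uses an unadjusted chi-square test and claims no gain from covariates.

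**The concern.** The endpoint is a cut-off on the same scale that decides entry. A patient who enters at 4 needs a fall of at least 2 points to reach a total of 2; one who enters at 10 needs at least 8. It is plausible that entry score predicts remission, and it should be on file for every randomized patient. The planned model uses none of this.

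In a logistic model, adjusting for a prognostic baseline variable usually raises the power of the treatment test and corrects the treatment contrast for chance imbalance in that variable. The hierarchy gives this some weight. FMFT, the novel arm, can be tested against placebo only after FMT has beaten placebo. In the 30/40/10% row of Table 1 that earlier step has only 69% power, against 95% for FMFT itself.

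**Working it through.** Rates are given in the order FMT/FMFT/placebo.

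**1. The plan's own figures.** For the global test, λ = n·Σ(pᵢ − p̄)² / [p̄(1 − p̄)] with 2 df. At 30/30/5%, p̄ = 0.2167, Σ(pᵢ − p̄)² = 0.04167 and p̄(1 − p̄) = 0.1697, so λ = 0.2455·n.
- n = 40: λ = 9.82, power 80.8% (n = 39 gives 79.7%). This agrees with "3 × 40 = 120 is required for the confirmatory analysis".
- 40/(1 − 0.30) = 57.1, rounded up to 58.
- n = 58: λ = 14.24, power 93.2% (stated 93).
- With continuity correction, combined versus placebo is 98.2% (stated 98) and one arm versus placebo 92.2% (stated 92).

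The other two rows of Table 1 also reproduce to within a point.

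**2. Assumptions needed.** The article gives no association between entry score and remission. I assumed odds ratios (OR) for remission of 1.0 to 3.0 per 1 SD lower score, with scores spread over 4 to 10 (mean about 6.9, SD about 1.6; 1.5 in the hierarchy runs). With SD 1.63, the full range spans 6/1.63 = 3.68 SD. Across that range, OR 1.5 per SD means 1.5^3.68 ≈ 4.4, OR 2 means about 13 and OR 3 about 57. The upper end is a generous assumption.

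**3. Power without → with baseline Mayo.** Simulated logistic models, Wald tests, 58 per arm, 3,000 to 5,000 trials per setting, stratum and site left out. With 3,000 trials the Monte Carlo standard error near 93% is √(0.93 × 0.07/3,000) ≈ 0.5 point.

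| Rates (%) | Test | OR 1.5 | OR 2 | OR 3 |
|---|---|---|---|---|
| 30/30/5 | global | 92.8 → 93.4 | 92.7 → 93.1 | 92.8 → 93.7 |
| 30/30/5 | FMT vs placebo | 91.9 → 92.4 | 91.9 → 92.3 | 91.6 → 92.6 |
| 30/40/10 | FMT vs placebo | 77.6 → 78.5 | 77.1 → 80.1 | 77.0 → 83.0 |
| 21/21/3.5 | global | 66.5 → 67.5 | 66.5 → 68.9 | 67.4 → 72.9 |

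The last row takes the planning rates as rates among observed patients and counts 30% dropout as non-remission: 0.7 × 30 = 21 and 0.7 × 5 = 3.5. The 77% for FMT at 30/40/10% exceeds Table 1's 69% because the table uses a continuity correction; without it the formula gives 77.5%.

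**4. Reaching and winning FMFT versus placebo through the hierarchy.**

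| Rates (%) | OR 1.5 | OR 2 | OR 3 |
|---|---|---|---|
| 30/30/5 | 86.9 → 87.7 | 87.4 → 88.6 | 86.6 → 89.7 |
| 30/40/10 | 75.0 → 76.4 | 76.0 → 79.1 | 77.0 → 82.8 |
| 21/21/3.5 | 51.8 → 53.9 | 52.1 → 56.5 | 52.7 → 62.0 |

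With a four-level stratum term in the model (site still left out), the gains ran from about 0 to 8 points at 30/40/10% and from about 2 to 9 points at 21/21/3.5%.

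**5. Cost when Mayo is not prognostic.** At OR 1.0 the global Wald power moves from 92.5 to 92.2% at 30/30/5%, stays at 94.5% at 30/40/10%, and moves from 66.3 to 65.9% at 21/21/3.5%. At OR 1.3 the changes are also within simulation error.

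**6. Type I error.** At a common rate of 20%, Wald tests reject in 3.3 to 4.2% of trials without the covariate and 3.7 to 4.6% with it.

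**7. Chance imbalance.** At 30/40/10%, about 7 to 10% of simulated trials had FMT patients entering more than 0.25 SD (about 0.4 Mayo point) worse than placebo. In those trials the power of FMT versus placebo was 68.6 → 79.3, 60.8 → 80.6 and 62.7 → 89.1% at OR 1.5, 2 and 3. Each figure rests on only about 210 to 300 trials, so its standard error is roughly 2 to 3 points. These trials were picked for an unfavourable imbalance; the opposite imbalance would flatter FMT in the unadjusted model.

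**8. Events available.** 58 × (0.30 + 0.30 + 0.05) = 37.7 remissions expected, of which 58 × 0.05 = 2.9 on placebo. At the diluted rates it is 58 × 0.455 = 26.4, of which 2.0 on placebo.

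**The case against.** The case against is substantial. The model carries the steroid/thiopurine factor and the centre that one of the stratification descriptions names, which is a defensible prespecified choice. Leaving out a prognostic covariate does not bias the test, and chance imbalance is already allowed for in the error rate. The decisive input, prognostic strength, is nowhere in the article. At the plan's own rates there is almost nothing to gain; the larger gains need a strong predictor together with either a weaker scenario or a dropout dilution that Table 1 does not apply. The model is already sparse: about 38 remissions, a four-level stratum and about 20 sites. The full GLMM with the site effect was not simulated.

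Most of this stands. It rules out calling the omission an error, and it rules out calling the gain free. It does not remove the suggestion. The 30/40/10% scenario is the plan's own, FMFT depends there on the weaker FMT comparison, and no setting examined showed a meaningful loss from the extra term.

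A reader might go further and infer that a modest imbalance in entry severity could decide the trial. The article does not support that: it gives no link between entry score and remission, and the imbalance figures above hold only under assumed links and in a selected minority of simulated trials.

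**Conclusion.** The point stands as an improvement to a prespecified model. The plan contains no mistake here: its sample-size figures reproduce and its test is valid without the covariate.

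The benefit is about 1 point or less of global power at 30/30/5%. It is larger, but still modest, for the FMFT claim through the hierarchy at 30/40/10% or under diluted rates. It is about zero if the odds ratio per SD is 1.3 or lower. These sizes rest on the assumed prognostic strength and score distribution, on Wald tests and on leaving out the site effect; the diluted case also assumes that the planning rates describe observed patients.

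Two stronger readings are tempting. One is that the trial gives up free power; the other is that entry score must be a strong predictor because the endpoint is a threshold. The threshold makes prediction plausible but does not measure it, and adjustment has a small price in parameters and interpretation.

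**What to change.** Before unblinding, prespecify baseline total Mayo score, as a continuous fixed covariate, in the primary GLMM. Do the same in the models for the Mayo-based secondary endpoints (steroid-free remission and clinical response), unless the full protocol already does so.

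Cost: one model term and no new data. The term adds one parameter to a model with few events. The treatment odds ratio becomes conditional on entry score, so an adjusted (standardised) risk difference should be reported beside it. The choice has to be made in advance, because adding the covariate after an imbalance has been seen would not be credible.

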## Strengths of this study

This multicenter study is the first randomized three-armed placebo-controlled trial assessing the clinical efficacy of sterile fecal microbiota filtrate transfer (<0.2 μm; FMFT) for treating active ulcerative colitis compared with classical fecal microbiota transfer (FMT).Videotaped colonoscopy with biopsies will be performed at study entry and 12 weeks after randomization to assess endoscopic and histological inflammatory activity. Central reading of video recordings will be performed.Patient’s reported quality of life indices will be assessed.Use of oral, frozen, encapsulated fecal microbiota or fecal microbiota filtrate for long-term treatment may increase patients’ acceptance.

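### The fixed test order makes confirmation of FMFT depend on FMT succeeding first, which three arms do not require for error control and which costs power for FMFT

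*Protocol article*

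**What the plan says.** The Statistical analysis section of the protocol article starts with a global test of treatment in a mixed model. If it rejects, "the following tests will be performed in a hierarchical order". The list runs: (1) FMT and FMFT combined versus placebo, (2) FMT versus placebo, (3) FMFT versus placebo, (4) FMFT versus FMT. Each is tested "by means of Wald statistic on a two-sided significance level of 0.05". The section adds: "The significance level is met by this hierarchical testing approach".

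The Sample size section gives powers at 58 patients per arm in Table 1. Its last column treats FMT versus placebo and FMFT versus placebo as separate comparisons, each by a "two group continuity corrected *χ*^2^ test of equal proportions". For true rates of 30% (FMT), 40% (FMFT) and 10% (placebo) it shows 92% for the global test, 95% for the combined comparison, 69% for FMT and 95% for FMFT. No power is given for the tests taken in sequence.

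**The concern.** In its usual meaning, a hierarchical order stops at the first non-significant test. The filtrate's comparison with placebo is then reached only if the global test, the combined comparison and FMT versus placebo have all succeeded. The Strengths section presents the filtrate as the novelty: "This multicenter study is the first randomized three-armed placebo-controlled trial assessing the clinical efficacy of sterile fecal microbiota filtrate transfer". If FMT is weaker than hoped, or merely unlucky, a filtrate with a clear effect could not be declared effective within the confirmatory procedure, and the order could not credibly be changed after unblinding. A reader of Table 1 would also not learn that the 95% for FMFT describes a test that the procedure may never reach. If the order protected the error rate, this would be a price worth discussing. With three arms it adds no protection beyond the global test.

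**Working it through.** **Inputs.** From the Sample size section: 58 patients per arm, the rates in Table 1, the continuity-corrected two-group test. From the Statistical analysis section: two-sided 5%, Wald tests, the global test and the order. From the Intervention section: 1:1:1 allocation. Site and stratum effects are not modelled.

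**1. Table 1 reproduced, row 30/40/10.**

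For a pair with rate difference d, the continuity correction is undone by n' = (58 − 1/d)²/58. Power is then Φ{[d√n' − 1.96√(2p̄(1−p̄))] / √(p₁(1−p₁)+p₂(1−p₂))}.

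- FMT: d = 0.20, n' = 53²/58 = 48.4; (1.392 − 1.109)/0.548 = 0.517; power 69.7% (stated 69%).
- FMFT: d = 0.30, n' = 54.67²/58 = 51.5; (2.153 − 1.200)/0.574 = 1.66; power 95.1% (stated 95%).
- Global test: noncentrality 58 × Σ(pᵢ − p̄)²/[p̄(1 − p̄)] = 58 × 0.04667/0.19556 = 13.84 on 2 degrees of freedom; power 92.5% (stated 92%).
- Combined versus placebo: 95.0% (stated 95%).

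The other rows also agree for global, combined and pairwise tests. Row 30/30/5 gives 93.2, 98.2 and 92.2% (stated 93, 98, 92). Row 40/40/10 gives 96.3, 99.1 and 95.1% (stated 96, 99, 95).

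**2. Bound from Table 1 alone.** Under the order, FMFT is confirmed only if all of the global, combined, FMT and FMFT tests reject. Its power therefore cannot exceed the smallest of 92, 95, 69 and 95%, which is 69% for the continuity-corrected test. Without the order, but with the global test kept, the ceiling is the smaller of 92 and 95%, which is 92%.

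**3. Exact power to declare FMFT different from placebo.** All outcomes of three binomials with 58 patients each were enumerated. Ordered means global, combined, FMT, then FMFT. Unordered means global, then FMFT.

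| Rates FMT/FMFT/placebo, % | Pairwise test | Ordered | Unordered | Loss, points |
|---|---|---|---|---|
| 30/30/5 | continuity-corrected | 89.9% | 93.9% | 4.1 |
| | Pearson | 93.9% | 95.9% | 2.1 |
| | Wald (logit) | 91.4% | 94.1% | 2.7 |
| 30/40/10 | continuity-corrected | 69.6% | 94.4% | 24.8 |
| | Pearson | 78.4% | 95.1% | 16.8 |
| | Wald (logit) | 75.0% | 94.0% | 19.0 |
| 40/40/10 | continuity-corrected | 92.2% | 95.4% | 3.2 |
| | Pearson | 95.4% | 97.0% | 1.6 |
| | Wald (logit) | 94.5% | 96.4% | 1.8 |

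Losses are taken from unrounded powers. The exact unordered figures lie above the 92% ceiling of step 2 because exact global power in row 30/40/10 is about 95%, against 92.5% in the approximation. In an assumed scenario that is not in the document, with FMT inert (10/40/10), ordered power would be about 1 to 3% against 96 to 97% unordered.

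**4. Why the order is not needed.** Let a be the FMT effect and b the FMFT effect against placebo. The four nulls are a + b = 0 (combined), a = 0, b = 0 and a = b. Each of the six pairs has the single solution a = b = 0, which is the global null. Any positive weighting of a and b in the combined comparison gives the same result. So every intersection of two or more nulls is the hypothesis that the global test already examines at 5%. By the closed testing principle, each comparison may be rejected when the global test and its own 5% test both reject, in any order, with strong familywise control.

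**5. Numerical check of the unordered procedure.** Under the global null (common rates of 5, 10, 20, 30 and 50%) the exact chance of any rejection is at most 5.02% across the three tests. With only FMT inert, false rejection of FMT versus placebo is at most 5.05%. The small excess over 5% comes from discreteness.

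**The case against.** The Statistical analysis section contains no false statement. A fixed sequence after a 5% global test does keep the level, and nothing there says that the order is the only way to do so. Testing FMT first also has a rationale in the Background: six positive placebo-controlled trials of FMT in ulcerative colitis, against five patients with recurrent CDI for the filtrate. The sample size rests on the global test, which the order does not affect. The plan expects similar rates in the two active arms, and at 30/30/5 the loss is small. All of this stands, and it limits the weight of the point.

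A reader might go further in two ways. One is to call Table 1's 95% for FMFT wrong. It is not: the column is labelled as the power of each test in its own setting, and the figure reproduces. The other is to quote 69% as the ceiling for FMFT in row 30/40/10 whatever the test. That ceiling belongs to the continuity-corrected planning test. The planned analysis uses Wald tests, for which ordered power is about 75%.

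The rule of stopping at the first failure is not spelled out. It is the usual meaning of the term, but the full protocol is not shown. What the objection does not supply is a benefit of the order: any comparison rejected under it is also rejected without it, so dropping it takes power from none of the four.

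**Conclusion.** The point holds as a recommended improvement, not as the correction of an error. The procedure is valid but needlessly restrictive for the filtrate. The cost is about 2 to 4 points of FMFT power at the expected 30/30/5, and about 17 to 25 points, depending on the test, in the 30/40/10 row that the plan itself presents as a slight change of assumptions. It would be larger still if FMT were nearly inert, which is an assumption of this review. Table 1's pairwise figures are sound but do not describe the ordered procedure.

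The conclusion assumes stopping at the first non-significant test, the global test kept at 5%, and valid model-based tests. The powers come from simple binomial comparisons without site or stratum effects, so the mixed-model figures may differ somewhat.

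**What to change.** Replace the ordered list with: *If the global test rejects at 5%, each of the four comparisons is tested at two-sided 5% without ordering (closed testing, three arms).* This is one sentence, to be settled before unblinding and carried into the full protocol if the same order stands there. It needs no more patients, keeps strong error control and lowers the power of no comparison. The global test must stay, because the error control now rests on it.

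If the sponsor wants the order for reasons of priority, keep it, say why, and add to Table 1 the FMFT power under the ordered procedure with the test named. For row 30/40/10 that is about 69% with continuity correction (69% as the bound from Table 1, 69.6% by exact enumeration) and about 75% with Wald.
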